## **ADVERSE AIRWAY EFFECTS OF INHALED NICOTINE FROM TOBACCO AND E-CIGARETTES**

The current protocol is part of a larger collaborator study between the Miami VA Medical Center and the University of Miami aimed at evaluating the toxicity of electronic cigarettes (ECs). This sub-study will specifically enroll active smokers at the Miami VA to compare the effects of switching from active smoking to e-cigs versus continuation of smoking. As a secondary outcome, we will evaluate the feasibility of using EC as a tool for weaning from tobacco use.

### **BACKGROUND AND SIGNIFICANCE**

**Importance of the problem:** Smoking has innumerable adverse effects on human health. From a respiratory point of view, chronic bronchitis and chronic obstructive pulmonary disease (COPD) in the US and Florida are predominantly due to either active or passive chronic tobacco smoke exposure. The pathogenesis of these conditions involves the induction of smoke-mediated inflammation, shown to be in part due to increased TGF- $\beta$  signaling (1-4). The recent introduction of electronic cigarettes (ECs) to provide habitual smokers a source of nicotine without the need to inhale tobacco smoke is thought to reduce toxicity to airway epithelial cells. The use of ECs decreases use of traditional cigarettes (5), diminishes nicotine withdrawal symptoms (6, 7), leads to opposite effects on exhaled NO levels compared to tobacco (8, 9), and may diminish stimulation of reward centers in the brain leading to less dependence due to the lack of other tobacco-derived chemicals (10). While this may be beneficial, the medical community's concerns over unregulated EC use leading to increased nicotine addiction (11, 12) appears warranted given the rapid rise in popularity amongst teenagers (13). The manufacturers of ECs tout comparative safety as a reason to switch from traditional tobacco cigarettes to their products. However the dearth of data supporting this claim led the FDA to issue warning letters to these companies (14).

For now, the World Health Organization recommends against EC use (15) until ECs have been properly evaluated. On the other hand, the American Association of Public Health Physicians (16) support the use of ECs as a means of "Harms Reduction" (17, 18) since ECs provide nicotine without the myriad of other toxic chemicals produced from burning tobacco. These recommendations are mostly due to theoretical considerations and expert opinion. Due to the novelty of these devices, many concerns of their safety on health and long-term nicotine addiction remain unanswered due to a lack of studies that comprehensively evaluate their toxicity.

Current studies on EC vapors are conflicting and reveal that they produce either similar (19-21) or reduced (6, 22) effects on systemic nicotine levels, carcinogen levels and cardiovascular effects compared to other nicotine replacement strategies. Side effects of ECs include mouth/throat irritation (23), vertigo (23), headaches (23), bronchospasm (8, 24) and nausea (25) similar to those found with approved nicotine replacement therapies (NRT).

ECs produce nicotine vapors of a particle size that deposit the vapor in the lower respiratory tract (26, 27), unlike the larger sized particles of approved inhalation NRT devices that remain in the oropharynx (28, 29). This fact may explain why EC vaping but not NRT use has been associated with lipoid pneumonia (30) and bronchospasm (8, 24). It raises concerns that the toxicity of components of EC such as diluents may have significant health risks (31), in addition to the known risks of nicotine alone (32). The lack of consistent results demands a full evaluation of EC toxicity.

In 2009, the FDA reported that a cartridge of an electronic cigarette contained diethylene glycol (33), even though other studies failed to identify this substance. The FDA testing also identified

[name] PI

ADVERSE AIRWAY EFFECTS OF INHALED NICOTINE FROM TOBACCO AND E-CIGARETTES

VERSION 3.3 09/28/2017

tobacco-specific nitrosamines in ECs (33). Both substances are known carcinogens. However, they can also be found in nicotine gums and nicotine inhalers (34). Other harmful substances were found as well, including acrolein (35). The French national consumer agency analyzed the vapor of ECs and found formaldehyde levels matching those from tobacco cigarettes (36). On the other hand, the test conditions did not necessarily mimic real life scenarios. Therefore, exposure systems mimicking real life situations with an appropriate evaluation of toxicity are desperately needed, especially since the use of ECs has increased dramatically in recent years. Our proposal is designed to answer this question by investigating the safety of ECs in primary cultures of normal human bronchial epithelial (NHBE) cells and in clinical trials with individuals who are non-smokers or who replace tobacco smoking with EC vaping.

ECs produce vapor mainly from propylene glycol (PG) or vegetable glycerin (VG) that are blended at different concentrations, making comprehensive testing more difficult, especially when considering additional flavoring (which will not be addressed in this proposal). There are three major types of ECs on the market:

- Mini (cig-a-like), available with 0, 6, 12, 18 and 36 mg/ml of nicotine.
- Mid-size (vapor pens), available with 0, 6, 12, 18, 24 and 36 mg/ml of nicotine.
- Advanced personal vaporizers (APV) or MODS that deliver more vapor per puff using the same e-liquid and nicotine concentrations.

Since the major difference between these devices is the amount of vapor produced per puff, in this sub study we will focus on a commonly used mid-sized EC: eVic® (Joyetech Co., Ltd., ShenZhen China) with variable nicotine concentrations depending on patient use.

## EXPERIMENTAL APPROACH

The study will evaluate the effects of inhaling EC vapor containing nicotine when used as a tobacco replacement tool. **By using active cigarette smokers as a comparator group, the study will increase our knowledge of whether the use of ECs is more or less harmful than continuation of tobacco smoking.** This study will examine the *in vivo* effects of EC vapors in nasal ion transport and TGF- $\beta$  levels as well as in serum inflammatory biomarkers.

As the primary endpoint, nasal ion transport will be assessed by nasal potential difference (NPD), which measures the voltage potential resulting from epithelial ion fluxes (both Na+ absorption and Cl and K+ secretion, see 37, 38) at the mucosal surface *in vivo*. In normal airway epithelia, Na+ absorption is the primary ion transport activity so that the resulting airway surface potential difference is negative with reference to the interstitium (39). Ion transport across nasal epithelia is representative for findings in distal airways (40, 41).

We also believe that NPD is a reasonably sensitive and minimally invasive biomarker for this study as discussed below. We will use NPD as a primary endpoint because changes in most clinical parameters will only be seen after months or even years of exposure. For that particular reason, there is a recent surge to find alternative biomarkers that may be used as surrogate endpoints in shorter clinical trials. Since NPD directly measures the changes in ion transport expected to influence mucociliary clearance (MCC) and therefore overall outcome and since changes of NPD measurements are indirectly linked to lung function changes and MCC in trials with cystic fibrosis patients (44, 45), we believe that NPD lends itself as a reasonable surrogate for MCC for this clinical trial.

As secondary endpoints, we will also measure TGF- $\beta$  levels in nasal secretions and expression in nasal cells to correlate these with the level of CFTR and CaCC-mediated Cl conductance (CFTR is known to show decreased function with elevated TGF- $\beta$ ) (42, 43). In addition plasma

samples will be collected to study systemic markers of inflammation as well as toxic substances that may result from vaping and smoking

#### EXPERIMENTAL DESIGN

The design is a smoking replacement trial, in which we will compare changes in upper airway ion transport and inflammation in smokers who switch to EC vaping versus subjects that continue to smoke tobacco cigarettes. In addition, we will use the trial design to evaluate the feasibility of using the EC as a means to quit tobacco use.

*Study population/recruitment.* We plan to study the effects of continuous EC vaping (3 months) in 30 active smokers that successfully switch to ECs (a smoking replacement trial). For this, we plan to enroll approximately 200 active smokers (screening phase), expecting that only one fourth will be able to stay abstinent from tobacco and keep exclusively vaping the ECs after a month. The 30 subjects who can remain tobacco-smoke free for the initial 4 weeks will undergo the study procedures, as >90% of them are likely to remain on ECs for the next few months (49) (as opposed to what is observed in a smoking cessation trial (48)). Twenty additional smokers who wish to continue to smoke will be enrolled as well for the comparator group. Subjects that actively smoke and have a history of at least 5 pack-years will be invited to participate. Exclusion criteria include HIV, marijuana use, COPD, asthma and other concomitant inflammatory pulmonary disorders, subjects with known pulmonary diseases including malignancies, subjects with prior thoracic surgery and subjects that used oral corticosteroids or antibiotics within the prior 3 months, subjects with allergies to study medications and subjects incapable of providing informed consent. Subjects must be in stable condition.

Subjects will be enrolled primarily in the pulmonary function test laboratory, pulmonary and primary care clinics. We will place IRB-approved advertisements in clinics if necessary. Recruitment will occur over a course of 5 years.

The study will have 4 Phases: transition, stability, weaning and surveillance.

*Phase I: transition from tobacco use to EC (4 weeks):* After signing informed consent, all subjects entering the screening phase will have pulmonary function testing (PFT) if none available in the prior month and we will record basic demographic and social history. After obtaining an initial blood sample (plasma), we will provide and instruct the subjects how to use the EC (eVic®). The nicotine content of the “e-liquid” provided (a PG:VG mix 50:50) will match the number of cigarettes smoked a day and will vary from subject to subject (see below for calculation). We will use the 12 mg/ml concentration e-liquid. During this “transition phase” period we will assess their success of abstaining from smoking tobacco. To monitor abstinence to tobacco smoking, subjects will be seen in person weekly for measurements of exhaled CO (ExCO), and venous COHb. ExCO > 6 ppm (50) or venous COHb >1.6% (51) will be considered the result of tobacco cigarette use. In addition, we will measure urinary marijuana with a qualitative test and if positive we will exclude the subject from the study. During those visits we will assess vaping compliance by downloading the vaping history of the EC using the myVapors® software, available from the EC manufacturer and will collect data regarding potential side effects. Subjects will be encouraged to transition solely to EC within the first 4 weeks. Blood draws for biomarker assessment will be performed in each visit of this phase.

*Phase II: Stability on EC (12 weeks):* In this phase, subjects will remain on EC use for three months. In this phase, all subjects will continue to use ECs at a stable nicotine concentration for additional 12 weeks. Tobacco use abstinence will be monitored every week as in the transition phase as detailed in Table 1. High ExCO levels will be confirmed with venous COHb if necessary. Oral washes and nasal lavages will be done at the beginning and the end of this phase.

Smoker controls: 20 tobacco smokers will be directly enrolled in the “stability” phase, where they will continue to use their regular tobacco for 3 months. They will undergo nasal samplings and NPDs before and after, with monthly blood collections. After this phase, these control subjects may be re-enrolled in the study to start in the transition phase with EC.

Inhaled nicotine dose calculation: We will match the subjects’ daily nicotine dose when switching from tobacco smoking to EC vaping. A Kentucky 3R4F research cigarette contains ~0.7 mg nicotine (<http://www2.ca.uky.edu/refcig/3R4F%20Preliminary%20Analysis.pdf>) and is consumed in 9 puffs. The equivalent of 1 pack per day (180 puffs, 14 mg of nicotine) would be an eVic® 1.2 ml cartridge containing 12 mg/ml of nicotine (cartridges are available as 6, 12, 18, 24, 36 and 48 mg/ml). One cartridge provides 180-200 puffs. Given that nicotine content in “e-liquids” is variable, we expect subjects to adjust their number of puffs or cartridges a day according to their needs or preferences. Since the EC chosen will count the puffs, we will have a record of use.

Statistical Analysis: An  $n = 50$ , 30 EC users and 20 smokers, gives us a power of >98% for detecting a difference in TGF- $\beta$  levels. We will analyze NPD parameters as described above. Results will be adjusted to nicotine exposure (urinary nicotine and cotinine levels) and inhalation (EC puffs per day).

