## PROCEDURES PERFORMED AT THE UNIVERSITY OF MIAMI

**Nasal potential difference (NPD) measurements:** This will be our primary outcome. Since tobacco smoke changes NPD, we will assess whether EC vapors with nicotine elicit a similar effect. Subjects will be instructed to exhale through the nose when vaping. NPD will be measured as previously described (47) and as detailed in Human Subjects. Effects on CFTR and CaCC-mediated ion transport will be evaluated. We will also collect nasal cells and lavages to measure TGF- $\beta$  levels (mRNA and protein by ELISA) and correlate these with the level of CFTR- and CaCC-mediated  $\text{Cl}^-$  conductance.

**Nasal lavages** will be performed using 10cc of normal saline will be harvested to measure inflammatory markers.

**Nasal brushings** will be performed to harvest nasal epithelial cells for assessment of mRNA changes (cytokines and other inflammatory molecules).

**Exhaled NO measurements** (breath and nasal) will be performed as a marker of inflammation.

**Plasma Cotinine levels measurements** 200ul of plasma of each study subject will be send to the **University of Miami Rosentiel Medical Science Building; Pulmonary Research Department Room # 7052.**

**Leukosorb collection of nasal fluid:** After 100  $\mu\text{L}$  normal saline will have been sprayed into the nose, a small paper will be inserted and the nostril closed with a nose clip for 2 minutes. Then, the paper will be retracted and eluted for cytokine analysis in the laboratory (56). No adverse effects are known.

The following **Table 1** outlines the timing of the above procedures in relation to study visits.

|                          |            | TRANSITION PHASE |        |        |        |                                | STABILITY PHASE |        |        |        |        |        |        |        |        |        |                         |
|--------------------------|------------|------------------|--------|--------|--------|--------------------------------|-----------------|--------|--------|--------|--------|--------|--------|--------|--------|--------|-------------------------|
| Time (weeks)             | E          | 1                | 2      | 3      | 4      | 5                              | 6               | 7      | 8      | 9      | 10     | 11     | 12     | 13     | 14     | 15     | 16                      |

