## EXPECTED RESULTS, POTENTIAL DIFFICULTIES, AND ALTERNATIVE STRATEGIES

The importance of this study design is that it mimics real world use of ECs. These devices are being widely promoted as an alternative form of smoking cessation with many switching to but not weaning from them. This is in part because of the unproven statement that tobacco-free products are safer and their indoor use is unregulated, which theoretically allows an increased nicotine exposure. For the trial, we chose to study the most commonly used EC type and the most frequently used e-liquid mix of PG and VG (50:50).

The effects of EC on airway TGF- $\beta$  and ion exchange are hard to predict at this point. We expect that the presence of nicotine will significantly affect NPD similar to what regular tobacco cigarettes do. If the PG:VG mix has no local toxic effects in this subacute exposure (determined in other aspects of the study), it is possible that TGF- $\beta$  levels will improve as the duration of tobacco cigarette abstinence increases (nasal samples), but nicotine could maintain these levels seen with smoking. If this is the case, it will provide valuable information that replacing regular cigarettes with EC is not less toxic or harmful as is generally perceived.

The initial phase of screening more smokers than required to complete the analysis is necessary to avoid performing semi-invasive and time consuming procedures such as NPD in subjects likely to relapse back to tobacco use, as well as to avoid the phase of dysregulated airway inflammation that may occur when smoking cessation occurs (55). Although the subjects undergoing study procedures will do so after 4 weeks of already using ECs, we expect to still detect significant differences in the data collected 3 months later if there is cumulative toxicity in the long term.

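### Adjusting for EC puffs per day, which is zero in every smoker control, turns the EC-versus-smoker difference into an imprecise extrapolation

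*Protocol*

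**What the plan says.** The contrast is set out under Experimental Design: changes in "smokers who switch to EC vaping versus subjects that continue to smoke tobacco cigarettes". Of the controls the same section says "20 tobacco smokers will be directly enrolled in the “stability” phase, where they will continue to use their regular tobacco for 3 months", and the planned-enrolment tables list them as smokers without e-cigarettes.

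The Statistical Analysis paragraph gives the sample size, "30 EC users and 20 smokers, gives us a power of >98% for detecting a difference" in TGF-β, and then the adjustment: "Results will be adjusted to nicotine exposure (urinary nicotine and cotinine levels) and inhalation (EC puffs per day". It states no effect size, SD, alpha or sidedness.

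The dose-calculation paragraph just before it equates one pack a day with 180 puffs and adds "One cartridge provides 180-200 puffs". It intends nicotine dose to be matched at the switch, but expects subjects to set their own puff count afterwards.

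On measurement, the University of Miami procedures say of cotinine that "200ul of plasma of each study subject will be send to the" university laboratory. The Miami VAMC procedures assay nicotine metabolites in exhaled breath condensate and plasma. The only urine test described is in Phase I: "we will measure urinary marijuana with a qualitative test".

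**The concern.** EC puffs per day is not a characteristic that the two groups share and on which they might be unbalanced. It is a consequence of being in the EC group and cannot be anything but zero in the controls. Entered beside group, it competes with group to explain the same difference. The fitted group effect is then the gap at zero puffs, where there are no EC users.

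At stake is the trial's main comparison. A real EC-smoker difference could be reported with an error far larger than the sample-size statement implies, and so be read as no difference. The sentence applies to results without qualification, so it covers the primary endpoint (NPD) as well as TGF-β.

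Two smaller questions come from the same sentence. On-study nicotine is also measured after the switch. And the urinary measure it names does not match the assays described.

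**Working it through.** **Inputs.** From the protocol: 30 EC users, 20 smokers, 180 puffs per day for a one-pack smoker, zero EC puffs in controls, power over 98%. Assumed: two-sided alpha 0.05, and a between-subject SD of puffs of 45 to 90 (36 and 120 shown as outer cases).

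**Step 1: the stated power.** It cannot be reproduced forwards, because no effect size or SD is given. Solved backwards for 98%:
- Normal approximation: (1.960 + 2.054) × √(1/20 + 1/30) = 4.014 × 0.2887 = 1.16 SD.
- t-test with 48 degrees of freedom: 1.18 SD.
- One-sided 0.05, normal: 1.07 SD.

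The value 1.18 SD is used below. The figure concerns TGF-β; this paragraph gives none for NPD.

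**Step 2: variance inflation of the group effect.** With a proportion p = 0.6 in the EC group, mean puffs m = 180 and standard deviation s, the share of puff variance explained by group is

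R² = p(1−p)m² / [p(1−p)m² + p s²], and VIF = 1/(1−R²).

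Here p(1−p)m² = 0.24 × 32,400 = 7,776.
- s = 45: 7,776/(7,776 + 1,215) = 0.865, VIF 7.4
- s = 60: 7,776/(7,776 + 2,160) = 0.783, VIF 4.6
- s = 90: 7,776/(7,776 + 4,860) = 0.615, VIF 2.6

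The finite-sample form, VIF = 1 + 12m²/(29s²) with 12 = 20 × 30/50, gives nearly the same values and is used for power.

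**Step 3: power at 1.18 SD when the effect does not depend on puffs** (noncentral t, 47 degrees of freedom; 98% without the covariate).

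| Assumed puff SD | VIF (finite sample) | Standard error multiplied by | Power |
|---|---|---|---|
| 36 | 11.3 | 3.37 | 22% |
| 45 | 7.6 | 2.76 | 31% |
| 60 | 4.7 | 2.17 | 45% |
| 90 | 2.7 | 1.63 | 69% |
| 120 | 1.9 | 1.39 | 82% |

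**Step 4: where the estimate is centred.** Simulation, 4,000 trials per setting, puff SD 45, 60 and 90:
- Effect independent of puffs: the adjusted estimate averages 1.14 to 1.18, against a true 1.18. Its SD rises from about 0.28–0.29 to 0.81, 0.63 and 0.49, and power is 29%, 44% and 67%.
- Effect wholly proportional to puffs: the unadjusted estimate averages 1.18 to 1.19 with 96% to 98% power. The adjusted estimate averages about zero and is significant in 5% to 5.5% of runs.

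In between, if a fraction f of the effect scales with puffs, the adjusted group coefficient averages (1−f) × 1.18.

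**Step 5: nicotine or cotinine as covariate.** VIF = 1 + 12δ²/48 for a group difference of δ within-group SDs: 1.06, 1.25 and 2.0 at δ = 0.5, 1 and 2. If matching works, δ is small and little precision is lost.

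**Step 6: urine or plasma.** The Statistical Analysis paragraph names urinary nicotine and cotinine. Both procedure sections name plasma for cotinine, and neither describes a urinary nicotine or cotinine assay. Table 1 has no row for one, but it also omits exhaled NO and Leukosorb sampling, which are described. The procedure text is therefore the better evidence.

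**The case against.** The strongest reply is that the sentence specifies no model. It does not say that group and puffs enter one regression, that the adjusted result is the main one, or that the unadjusted comparison is dropped. A within-EC puff analysis might be meant, and a SAP, not shown, could say so. This stands as a reason to clarify. It does not rescue the text: the paragraph is about the comparison of 30 with 20, and no reading that keeps puffs in that comparison is sound. Normalising results per puff would be undefined for all 20 controls.

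A reader might infer that the adjustment makes a real EC effect vanish. The documents do not support that as a general statement. It requires the whole EC-smoker difference to scale with puffs, so that an abstinent ex-smoker taking no puffs would resemble a continuing smoker. The contrast also includes stopping tobacco, and the Expected Results section allows TGF-β to improve with longer abstinence.

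A reader might also infer that adjusting for nicotine removes the effect under study. The protocol does say "We expect that the presence of nicotine will significantly affect NPD similar to what regular tobacco cigarettes do". But both groups take nicotine, the dose is meant to be matched, and the quoted expectation is of a similar effect, not a different one. A comparison at equal nicotine is a legitimate, different question. What remains is that matching is not assured and that the question should be labelled.

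Self-selection of successful switchers is a separate matter, and comparing changes handles part of it. Nor is it right that no urine is obtained: it is, for the marijuana screen.

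**Conclusion.** The concern holds for EC puffs per day. The covariate is structurally zero in controls, and keeping it in the between-group comparison inflates the variance of the group effect 7.4- to 2.6-fold at assumed puff SDs of 45 to 90. Against the effect implied by the stated power, that leaves about 31% to 69% power if the effect does not depend on puffs. In that case the loss is of precision, not bias; bias towards zero arises only in proportion to any dependence on puffs.

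These sizes rest on the assumed puff SD, a mean of 180, two-sided 0.05 and a linear model. That the covariate is zero in every control rests on none of them.

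Nicotine adjustment is a lesser point, conditional on how well dose is matched. The urinary-versus-plasma mismatch is real but small.

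**What to change.** Replace the adjustment sentence with one paragraph that does the following:

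- Removes EC puffs per day from the EC-versus-smoker comparison and uses it only for dose-response within the EC group.
- Makes the main comparison one of change over the stability phase, without on-study nicotine or cotinine. It should be adjusted for the outcome value at the first NPD visit and one or two pre-switch variables, such as cigarettes per day or pack-years. With 50 subjects the list should stay that short. In the EC group the first NPD visit follows four weeks of vaping, so the text should state that this comparison concerns the 12 weeks after it.
- Labels any plasma-cotinine-adjusted model as secondary, a comparison at equal nicotine.
- Reconciles urinary with plasma, either by changing the word or by describing a urinary assay and adding it to Table 1.

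The cost is a paragraph of text, recording the chosen pre-switch variables in the controls too, and one or two degrees of freedom for those variables plus one for the first-visit value. This is partly offset by those no longer spent on puffs and nicotine.
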